### Sample size {14}

In previous studies, the incidence rate of myelosuppression was 81.0% in the control group and 61.7% in the TCM decoction group [29]. The cure rate and effective rate of the moxibustion group were 84.1% and 66.4%, while those of the control group were 35.2% and 33.3% [30]. In our preliminary study, the bone marrow suppression rate (grade 2 or above) was 52% and 81% for the MD group and the control group, respectively (δ = 15%in superiority trial). Since there are no previous data supporting the combination use of moxibustion and TCM decoction, the sample size calculation was simply based on MD/MP group versus control group, assuming that the effect of combination treatment is equivalent to or better than moxibustion or decoction alone. Considering patient enrolment at a ratio of 1:1:1 for the control, MD, and MP groups, the sample size is calculated by multiple sample rate comparisons. The sample content estimation formula is as previously described [31]. Given that *α* = 0.05 and 1-*β* = 0.08, taking a 20% drop rate into account, the required total sample size is 462 cases and 154 cases in each group.

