## Statistical methods

### Statistical methods for primary and secondary outcomes {20a}

Data were analysed using SPSS 18.0 (SPSS, lnc., Chicago, IL) and Stata10.0 (StataCorp, College Station, Texas). Multivariate analysis was performed by multiple linear regression, COX regression, or logistic regression, where appropriate. All analyses are based on two-sided test, with *P* values < 0.05 considered as statistically significant.

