#### Categorical variables

The frequency, relative number, and rate of the data will be calculated. If the data is not in order, the chi-square test or Fisher’s exact test is used to compare the difference between groups. If the data is in order, the rank-sum test is used instead.

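### The sample-size paragraph states a power of 0.08, which cannot yield 154 per arm, and cites a 15-point superiority margin that the planned two-sided tests never examine

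*Protocol article*

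**What the plan says.** The Sample size {14} section of the protocol article offers several sets of rates. Two concern the incidence of myelosuppression: 81.0% v 61.7% from an earlier decoction study, and 81% v 52% (grade 2 or above, control v MD) from the team's preliminary study. The second pair is followed by the parenthesis "δ = 15%in superiority trial". The section says the calculation rests on MD/MP against control with 1:1:1 allocation, and that "the sample size is calculated by multiple sample rate comparisons", with the formula given by citation only. It sets α at 0.05 and closes with "1-*β* = 0.08, taking a 20% drop rate into account, the required total sample size is 462 cases", 154 per group. It does not say which rate pair was used, whether α is one- or two-sided, or whether δ entered the formula.

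Statistical methods {20a} states "All analyses are based on two-sided test, with *P* values < 0.05 considered as statistically significant". Under Categorical variables, for unordered data, "the chi-square test or Fisher’s exact test is used to compare the difference between groups". No section describes a test or confidence interval set against 15 points.

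**The concern.** Two things are wrong on the face of the text. First, 1-β is power, and 0.08 cannot be the power intended. The slip could stand for a power of 0.80 or for β = 0.08 (power 0.92), and the reader cannot tell which. Second, a superiority margin belongs to a different hypothesis from the one the analysis tests. A significant chi-square test shows that two rates differ. It does not show that they differ by more than 15 points.

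At stake is the justification for enrolling 462 patients. As printed, nobody can say what effect, hypothesis and power the trial was sized for. A later reader could also attach the 15-point wording to a result that only excludes zero.

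**Working it through.** **Inputs.** From Sample size {14}: control 81%; MD 52% or decoction 61.7%; δ = 0.15; α = 0.05; 20% loss; 154 per arm. From Statistical methods {20a}: two-sided tests. Evaluable per arm after 20% loss: 154 × 0.8 = 123.2, taken as 123.

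Sum of variances, 81% v 52%: 0.81×0.19 + 0.52×0.48 = 0.4035. For 81% v 61.7%: 0.81×0.19 + 0.617×0.383 = 0.3902.

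**1. The power as printed.** With power 0.08, z = −1.405. Two-sided 0.05, 81% v 52%, against the margin: (1.960 − 1.405)² × 0.4035 / (0.29 − 0.15)² = 6.3, so 7 per arm. Without a margin the same formula gives 2 per arm (81% v 52%) or 4 (81% v 61.7%). None is near 154.

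**2. The method as named.** Assumption: the usual arcsine formula for several proportions, n = 2λ/(2·asin√p₁ − 2·asin√p₂)², with three groups (2 df). At α = 0.05 and 80% power, λ = 9.63.
- 81% v 52%: 2 × 9.63 / 0.6287² = 48.7, so 49. With the allowance: 49/0.8 = 61.25, so 62.
- 81% v 61.7%: 2 × 9.63 / 0.4326² = 103.0, so 103. With the allowance: 103/0.8 = 128.75, so 129.
- At power 0.92 the evaluable numbers are 69 and 146, which become 87 and 183.

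None of these is 154.

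**3. Calculations that do reach about 154.**

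| Rates | Hypothesis and settings | Evaluable | Inflation | Enrolled |
|---|---|---|---|---|
| 81% v 52% | margin 15 points, one-sided 0.05, power 0.80, unpooled | 127.3, so 128 | ×1.2 = 153.6 | 154 |
| 81.0% v 61.7% | zero difference, two-sided 0.05, power 0.92 | 121.9, so 122 | /0.8 = 152.5 | 153 |
| 81.0% v 61.7% | zero difference, two-sided 0.05, power 0.90, continuity correction | 123.4, so 124 | /0.8 = 155 | 155 |
| 81.0% v 61.7% | 2-df arcsine, α = 0.025, power 0.80 | 122.9, so 123 | /0.8 = 153.75 | 154 |

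The first row is (1.645 + 0.842)² × 0.4035 / 0.14² = 127.3. With division by 0.8 it gives 128/0.8 = 160, not 154. Each row needs at least one setting that the section does not state.

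**4. Power at 123 evaluable per arm.**
- Planned test (two-sided 0.05, zero difference, one arm v control): 99.9% for 81% v 52% and 92.2% for 81.0% v 61.7%. An overall three-group chi-square test with both active arms at the lower rate gives nearly the same: 99.9% and 92.9%.
- Two-sided 0.05 against 15 points, 81% v 52%: SE = √(0.4035/123) = 0.0573; Φ(0.14/0.0573 − 1.960) = 0.686.
- One-sided 0.05 against 15 points: Φ(0.14/0.0573 − 1.645) = 0.788.

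**5. What each criterion demands of the data.** For the two-sided 95% interval to lie above 15 points, the observed difference must be about 0.15 + 1.96 × 0.0573 = 0.262, or 26 points. With control at 81%, the zero-difference test is already significant at about 11 points: 0.11/√(2×0.755×0.245/123) = 2.01.

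**6. What the margin would cost at 80% power, two-sided.** (1.960 + 0.842)² × 0.4035 / 0.14² = 161.6, so 162 evaluable; 162/0.8 = 202.5, so 203 enrolled per arm, or 609 in total.

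**The case against.** The best reply is that 0.08 is a plain misprint, that the formula sits in a source not shown here, and that the trial is not short of patients for the test it plans: power is at least about 92% on either rate pair. All of that stands. It means the number 462 need not change, and that the actual derivation may be coherent.

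A reader who finds that the one-sided margin calculation lands exactly on 154 might infer that this is how the trial was sized. On that reading the protocol sized one-sided and analyses two-sided, and it inflated for drop-out wrongly by multiplying by 1.2. The documents do not support that. The section states neither a one-sided α nor how the 20% was applied, and three zero-margin calculations on the other rate pair give 153 to 155 with ordinary division by 0.8. One of them uses the named type of method and gives 154 exactly, although at α = 0.025 rather than the stated 0.05. A sidedness conflict and a drop-out error would be faults of a guessed derivation, not of the text.

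Nor does the text say outright that superiority by 15 points will be claimed. It has only the parenthesis after the preliminary rates. The reply does not remove the wrong power, or the presence of a margin with no counterpart in the analysis.

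**Conclusion.** The point holds in this limited form. The stated power is wrong and incompatible with 154 per arm. The named method at the stated α does not give 154 at 80% power under the standard formula. The 15-point margin is not tested anywhere in the analysis. Because several incompatible designs reach about 154, the rate pair, sidedness, power and role of δ cannot be inferred.

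The size of the problem depends on what δ means. If it plays no part, this is a reporting error in a trial with ample power for its planned test. If it is the intended claim, the two-sided power is about 69% at 123 evaluable per arm, and a significant chi-square test would not establish the claim.

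These figures assume 20% loss in every arm, the rates quoted in the section, normal approximations, and, for the named method, the 2-df arcsine formula in place of the cited one. The text must be corrected, but the finding does not show that the trial is too small for the analysis it describes.

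**What to change.** Keep 462 patients and rewrite the Sample size {14} paragraph:

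1. Replace 1-β = 0.08 with the power actually meant.
2. State the rate pair, the sidedness of α, the formula, how the 20% was applied, and whether δ entered. Retain the multiple-rate description if that was the method, with the inputs that reproduce 154.
3. Settle δ in one of two ways.
   - **δ is not tested:** delete it, and state the power of the planned two-sided zero-difference test at 123 evaluable per arm for both rate pairs: about 92% for 81.0% v 61.7% and 99.9% for 81% v 52%. Quoting only the second would rest the trial on its most favourable assumption.
   - **δ is meant:** add to the analysis of rates that superiority is claimed only when the lower limit of the two-sided 95% confidence interval for the MD-control risk difference (in the direction of benefit) exceeds 15 points, and state power of about 69% at 123 evaluable per arm (81% v 52%).

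The cost is one paragraph, plus one sentence in the statistical methods under the second choice, and no extra patients. The second choice makes the stated power less favourable. Trial status reports that recruitment is under way and outcome assessment is not blinded to the physicians, so the choice should be dated and recorded as made without sight of results by group.

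### On the protocol's preliminary rates and 15% margin, 154 per arm does not cover the stated 20% drop-out: 123 remain, against 128 needed one-sided or 162 two-sided

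*Protocol article*

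**What the plan says.** All inputs but one come from the section Sample size {14} of the protocol article.

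- Preliminary rates: "the bone marrow suppression rate (grade 2 or above) was 52% and 81% for the MD group and the control group, respectively".
- Margin: "δ = 15%in superiority trial".
- Error rates: "Given that *α* = 0.05 and 1-*β* = 0.08". The sidedness of α is not given here.
- Comparison and allocation: "the sample size calculation was simply based on MD/MP group versus control group" and "Considering patient enrolment at a ratio of 1:1:1 for the control, MD, and MP groups".
- A second pair of rates, from an earlier study: "the incidence rate of myelosuppression was 81.0% in the control group and 61.7% in the TCM decoction group".
- Result: "taking a 20% drop rate into account, the required total sample size is 462 cases and 154 cases in each group".

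The formula is named as one for comparing several rates and is given by citation only. The number per arm before the drop-out allowance is not printed, nor is the way the allowance was applied. The section Statistical methods for primary and secondary outcomes {20a} adds: "All analyses are based on two-sided test".

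**The concern.** An allowance for 20% drop-out should mean that the required number is still there after 20% are lost, so the evaluable number is divided by 0.8. Multiplying by 1.2 is a common slip, and it covers only 1 − 1/1.2 = 16.7%. The printed 154 is what that slip produces from the requirement implied by the section's own rates and margin.

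The loss bears directly on the evaluable number here. Under Strategies to improve adherence {11c}, outcome collection ends for participants who stop treatment and withdraw. If 154 falls short after exactly the planned loss, the article presents the trial as protected against something it is not protected against, and the planned power is slightly overstated.

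**Working it through.** **Inputs.** Control rate 0.81, decoction plus moxibustion rate 0.52, margin 0.15, α = 0.05, equal arms and drop-out 20% are all from Sample size {14}. Power is printed as 0.08, which cannot be a design power; I read it as 0.80. Sidedness is tried both ways.

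**Formula.** Superiority by a margin, two proportions, unpooled variance:

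n = (z_α + z_0.80)² × [p₁(1 − p₁) + p₂(1 − p₂)] / (p₁ − p₂ − δ)²

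Variance term: 0.81 × 0.19 + 0.52 × 0.48 = 0.1539 + 0.2496 = 0.4035. Difference beyond the margin: 0.29 − 0.15 = 0.14.

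**Reproducing the printed figure (one-sided 0.05).**
- n = (1.645 + 0.842)² × 0.4035 / 0.14² = 127.3, so 128 per arm.
- 128 × 1.2 = 153.6, so 154 per arm, and 3 × 154 = 462. Both printed figures match.
- 128 / 0.8 = 160 per arm, or 480 in total, which is 18 more than 462.

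**Two-sided 0.05, as {20a} requires.**
- n = (1.960 + 0.842)² × 0.4035 / 0.14² = 161.6, so 162 per arm.
- 162 / 0.8 = 202.5, so 203 per arm, or 609 in total.

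**What 154 per arm delivers after a 20% loss.** 154 × 0.8 = 123.2, so 123 per arm. Power is Φ(0.14 / √(0.4035/n) − z_α):

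| Evaluable per arm | One-sided 0.05 | Two-sided 0.05 |
|---|---|---|
| 123 | 78.8% | 68.6% |
| 128 | 80.2% | 70.3% |
| 154 (no loss) | 86.2% | 78.1% |

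One-sided, 123 is 5 short of 128, and 154 tolerates a loss of at most 1 − 128/154 = 16.9%. Two-sided, 154 is below 162 even with no loss.

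**Is the ×1.2 step the only route to 154?** No. Take the three-group arcsine formula, n = 2λ / (2 arcsin√p₁ − 2 arcsin√p₂)², with 2 degrees of freedom, 81.0% against 61.7%, no margin, 80% power and α = 0.025. Then λ = 11.49, the arcsine difference is 0.4326 and n = 122.85, so 123. Dividing, 123 / 0.8 = 153.75, so 154 and 462. With the printed α = 0.05 the same formula gives 102.99, so 103, and 103 / 0.8 = 128.75, so 129, which does not match.

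**The case against.** The strongest reply is that the multiplication by 1.2 is nowhere in the text. It is inferred from a numerical match, and the match is not unique. The arcsine reading reaches 154 by a correct division, belongs to the family of methods that the section names, and makes 123 evaluable exactly the requirement. The section also says that data on the combination are lacking, which could point to the single-treatment rates. The route through 128 has unstated choices of its own: a one-sided α against the two-sided rule in {20a}, a two-group margin formula, and rounding up before inflating (unrounded, 127.28 × 1.2 = 152.7, so 153). The margin also carries the shortfall: with 81% against 52% and no margin, 123 per arm give 99.9% power at two-sided 0.05.

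What stands is this. A reader might infer that the protocol demonstrably multiplied by 1.2, or that 154 is too few on any reading. The document supports neither, since the base and the step are not printed.

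What does not stand is that the rival reading clears the printed figures. It replaces the printed α = 0.05 by 0.025 and sets aside both the printed margin and the 52% rate. It explains how 154 might have arisen; it does not make 154 sufficient for the preliminary rates and margin that the section states.

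Nor is this a detail that a condensed article may leave to the full protocol. The point concerns a printed total and a printed allowance that do not agree on the printed inputs.

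**Conclusion.** The point holds conditionally. On 81% against 52% with a 15-point margin and power read as 80%, 154 per arm does not cover a 20% loss. The one-sided reading is the more favourable to the sponsor, and there the gap is small: 5 patients per arm and 1.4 points of power (80.2% to 78.8%). Under the protocol's own two-sided rule the gap is 39 per arm (162 − 123) and power is 68.6%; most of that comes from the sidedness, not from the drop-out step.

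That the cause was multiplying by 1.2 is the likeliest explanation, because it returns 154 and 462 exactly from the stated rates and margin, but it remains an inference. The conclusion rests on three assumptions: the preliminary rates and the margin were the design inputs, 0.08 is a misprint for 0.80, and the two-proportion margin formula was used. This is a minor correction to a stated figure and no reason to doubt the design.

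**What to change.** In Sample size {14}, print the uninflated number per arm and the rates, margin, sidedness, power and inflation step actually used.

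If the base is 128, restate the allowance: 154 per arm covers about 17% loss, and a 20% loss leaves 123 per arm, with power about 79% at one-sided 0.05 or about 69% at the two-sided 0.05 of {20a}. The 79% should not appear without its one-sided condition, since it would then contradict {20a}. If another base was used, printing it with its inputs settles the matter equally well.

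The cost is a sentence or two. No patients are added and the design does not change; the stated figure becomes somewhat less favourable.

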### Recruitment {15}

None.

## Assignment of interventions: allocation

### Sequence generation {16a}

The administrative staffs are responsible for generating the random allocation sequence using SPSS and providing the treatment allocation to the physicians in sealed envelopes.

### Concealment mechanism {16b}

As mentioned above in {16a}.

### Implementation {16c}

The physicians are responsible for patient enrollment and the assignment of participants to corresponding interventions according to the treatment allocation.

## Assignment of interventions: blinding

### Who will be blinded {17a}

Participants in the MD and MP groups are blinded to the use of TCM. The required amount of TCM granule or TCM placebo will be provided to the corresponding participants according to the grouping each time after chemotherapy. In consideration of the patient’s safety, outcome assessments are not blinded to the physicians.

### Procedure for unblinding if needed {17b}

None.

## Data collection and management

### Plans for assessment and collection of outcomes {18a}

Paper-based case report forms are filled by the physicians and are securely delivered to the trial office by each corresponding physician as soon as possible. The filled data is double-checked by administrative staffs who are responsible for data entry and maintenance of the electronic database. Data will only be accessible to the physicians responsible for the data analysis after the completion of patient recruitment. The template of case report form is available upon request.

#### Baseline information

Baseline information including age (below 40s, 40–60s, 60s, or above), surgical approach (breast-conserving and axillary conserving), chemotherapy regimen (anthracyclines, taxanes, anthracyclines + taxanes, and others), chemotherapy strategy (adjuvant and neoadjuvant), pathological staging (stages I, II, III), and molecular subtype (Luminal-like, HER-2 positive, and Basal-like) will be recorded.

#### Short-term efficacy

Blood routine test: Monitoring WBC count and ANC once a week during every cycle of chemotherapy.TCM-related symptom: The investigators will evaluate the TCM-related symptoms based on the scoring method (Table 3) described in “Chinese Medicine New Drug Clinical Research Guidelines (Trial)” (China Medical Science and Technology Press, 2002) every 3 months.Adverse effects: Grading on a scale of 0 to 4 according to CTCAE 4.0.2.Quality-of-life: EORTC QLQ-C30, QLQ-BR23, and TCM Constitution.

**Table 3 Tab3:** Schedule of enrolment and assessment

	Baseline	During chemotherapy (every cycle)	Follow-up after chemotherapy (month)				
	0	1–8	6	12	18	24	36
Enrolment							
Informed consent	√						
Eligibility	√						
General assessment							
Age	√						
Sex	√						
Height	√						
Weight	√	√					
Body surface area	√						
Surgical approach	√						
Chemotherapy regimen	√						
Chemotherapy strategy	√						
Pathological stage	√						
Molecular subtype	√						
ECOG PS	√	√	√	√	√	√	√
EORTC QLQ-C30	√	√					
EORTC QLQ-BR23	√	√					
TCM constitution	√	√					
Chest CT	√			√		√	√
*Breast MRI	√			√		√	√
Serum tumour biomarkers	√	√	√	√	√	√	√
Key evaluation							
Blood routine test	√	At least once per week	√	√	√	√	√
Safety examination							
Urine routine test	√	√	√	√	√	√	√
Liver function (ALT, AST, ALP, TBIL, GGT, etc.)	√	√	√	√	√	√	√
Kidney function (CR, BUN, SCR, UA, etc.)	√	√	√	√	√	√	√
Electrocardiogram	√	√	√	√	√	√	√
Adverse events		√	√	√	√	√	√
Data evaluation							
Audit medical records		√	√	√	√	√	√
Ombudsman reviews medical records		√	√	√	√	√	√
Outcome measures		√	√	√	√	√	√

*MRI assessments were conditionally performed according to the patient’s disease status

All results are recorded in the case report form. Participants who show any adverse effects will be reported and followed up by their responsible physicians.

#### Long-term efficacy

Three-year, 5-year, and 10-year DFS and OS.Safety evaluation: Blood pressure, heart rate, heart rhythm, respiratory rate, blood routine test, and liver and kidney functions are assessed on a scale of four levels.
Level 1: Safe—no adverse reactions; no abnormalities in safety indicators.Level 2: Comparatively safe—mild adverse reactions are observed; treatment can be continued without any intervention; no abnormality in safety indicators.Level 3: Safe issues arise—moderate adverse reactions or mild abnormalities in safety indicators are observed; treatment can be continued with suitable intervention.Level 4: Serious adverse reactions—study abortion due to serious adverse reactions; safety indicators are remarkably abnormal.

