#### rhG-CSF

The rhG-CSF is performed according to the guidelines [12–14]. Patients with grade 1 myelosuppression according to the CTCAE 4.0.2 criteria are follow-up for both the intervention group and the control group. Patients with grade 2 or above myelosuppression should receive rhG-CSF treatment until the WBC count and ANC return normal. Two types of adjuvant chemotherapy regimens in breast cancer, namely ddAC-wP and TAC, can lead to a high risk of FN (incidence > 20%). According to the NCCN guidelines, prophylactic rhG-CSF treatment is recommended on day 2 or days 3 to 4 after chemotherapy. In detail, 5 mcg/kg is administrated per day until neutrophil count returns normal or nearly normal level, or long-acting rhG-CSF (PEG-rhG-CSF) is given on the second day after chemotherapy.

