### Outcomes {12}

#### Primary outcomes

Primary outcomes are as follows:
The proportion of patients with relief of leukopenia and/or neutropenia.The number and proportion of patients with relief of myelosuppression-associated SAE, defined as grade 3–4 leukopenia and/or neutropenia and FN.The median and mean duration time of relief of leukopenia and/or neutropenia.The dosing of rhG-CSF.

The grading of adverse reactions is in accordance with the CTCAE 4.0.2 criteria. Leukopenia is defined as an abnormal decrease in white blood cells of less than LLN-3.0 × 10^9^/L. Neutropenia is defined as an abnormal decrease in netrophils of less than LLN-1.5 × 10^9^/L. The definition of FN is based on the IDSA guidelines (American Society of Infectious Diseases Guide 2010 edition), which is an absolute neutrophil count (ANC) of < 500 neutrophils/mcL or an anticipated decline to ≤ 500 in the next 48 h and progress to ≥ 38.3 °C orally or ≥ 38.0 °C for a duration over 1 h.

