#### Secondary outcomes

Secondary outcomes are as follows:
Chemotherapy adherence: The percentage of patients who completed the full-course chemotherapy in a standard dose. If only the full course of treatment is completed but the dose of chemotherapy is reduced, or the dose is unchanged but the course of treatment is shortened, the case will be treated as poor adherence.Stratified analysis: Subgroup analysis will be done according to age, chemotherapy regimen, and chemotherapy strategy.Adverse events: Any toxic side effects such as general condition, gastrointestinal reactions, liver and kidney function, skin reactions, burns, and heat syndrome will be recorded.ECOG PS: The performance status of the patients before and after the completion of the whole treatment cycle according to the Eastern Cooperative Oncology Group.Quality-of-life survey: EORTC QLQ-C30 (V3.0) and EORTC QLQ-BR23 will be used to assess the QoL of patients. QLQ-C30 is a scale developed by the European Organization for Research and Treatment of Cancer (EORTC) to measure the QoL of cancer patients. QLQ-BR23 is a QoL questionnaire designed for breast cancer patients, which is suitable for evaluating all breast cancer patients regardless of the type of treatments. Also, a TCM Constitution survey based on the judgement criteria recognized by the China Association of Chinese Medicine will be conducted [28]. The TCM Constitution is assessed by filling out the “the Criteria of Classification and Judgment of TCM Constitution (ZYYXH/T157-2009)” (Table 1). Every patient is designed to respond to the questionnaire three times: (1) before chemotherapy initiation, (2) during mid-term chemotherapy, and (3) before the last cycle of chemotherapy. All assessments will be completed the day before chemotherapy administration.Survival: The differences in 3-year DFS and OS between the treatment group and the control group will be analysed.

**Table 1 Tab1:** “The Criteria of Classification and Judgment of TCM Constitution” scale

Classification	Conditions	Judgement
Normal constitution	A conversion score of ≥ 60, and conversion score of < 30 in all other 8 types	Yes
	A conversion score of ≥ 60, and conversion score of < 40 in all other 8 types	Generally yes
	Unsatisfied for the above conditions	No
Abnormal constitution	A conversion score of ≥ 40	Yes
	A conversion score of 30 to 39	Likely yes
	A conversion score of< 30	No

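### The four-level safety scale includes the routine blood test that also measures efficacy, so an arm with less myelosuppression can be rated safer and moderate intervention harm can be masked on this scale

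*Protocol article*

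**What the plan says.** The safety evaluation stands under Long-term efficacy in the protocol article: "Blood pressure, heart rate, heart rhythm, respiratory rate, blood routine test, and liver and kidney functions are assessed on a scale of four levels". Levels 1 and 2 both require that no safety indicator is abnormal. Level 3 applies when "moderate adverse reactions or mild abnormalities in safety indicators are observed" and treatment can go on with some remedy. Level 4 is worded as "study abortion due to serious adverse reactions; safety indicators are remarkably abnormal". The article gives no time point for the scale, and it does not say whether a patient gets one overall level or one level per indicator.

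The same blood test is the first item under Short-term efficacy: "Monitoring WBC count and ANC once a week during every cycle of chemotherapy". The primary outcomes rest on it, beginning with "The proportion of patients with relief of leukopenia and/or neutropenia" and going on to "myelosuppression-associated SAE, defined as grade 3–4 leukopenia and/or neutropenia and FN". The schedule in Table 3 puts the routine blood test in the Key evaluation block. Urine, liver, kidney and ECG tests stand apart from it under Safety examination.

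Harms are also collected outside the scale. The secondary outcomes state: "Any toxic side effects such as general condition, gastrointestinal reactions, liver and kidney function, skin reactions, burns, and heat syndrome will be recorded". The Short-term efficacy section grades adverse effects from 0 to 4 by CTCAE.

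**The concern.** A safety scale should show what the interventions do to patients apart from the benefit being tested. Here one of its indicators is the efficacy measurement. If moxibustion with decoction works as hoped, fewer of its patients have abnormal counts, and fewer reach Level 3 for that reason alone. The scale then credits the same effect a second time, as safety.

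Masking follows from this. A moderate burn or skin reaction also leads to Level 3, but a patient already there because of low counts does not move. In the combination arm such harms add to a smaller starting proportion, and the total can stay below control even when harm is common. The level labels are themselves verdicts on safety, so a reader could take the comparison at face value and conclude that the combination is safer.

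**Working it through.** No figure in the article is in dispute. The check is how the scale behaves at the article's own planning rates.

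**Inputs**
- Grade 2 or above myelosuppression, from the preliminary study under Sample size: 52% with decoction plus moxibustion (MD), 81% in control.
- Alternative rates from the earlier decoction study cited in the same section: 61.7% with decoction, 81.0% in control. No grade is given for these.
- Group size: 154.

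**Assumptions, none of them stated in the article**
- Each patient gets one level, assigned during chemotherapy.
- Every count of grade 2 or above is at least a mild abnormality, and grade 1 is not counted.
- The intervention causes moderate harm in a fraction *h* of MD patients, independently of their counts, and in no control patients.

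**Step 1: counts alone.** The rules for Levels 1 and 2 exclude any abnormal indicator, so 81% of control and 52% of MD are at Level 3 or higher. The apparent safety advantage is 81 − 52 = 29 percentage points, with no information on harm in it.

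**Step 2: add harm in MD.** P(Level 3 or higher in MD) = 1 − (1 − 0.52)(1 − *h*) = 1 − 0.48(1 − *h*). At *h* = 10% this is 1 − 0.48 × 0.90 = 56.8%.

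| Harm *h* in MD | MD at Level 3+ | Control at Level 3+ | Same comparison without blood counts (MD vs control) |
|---|---|---|---|
| 0% | 52.0% | 81% | 0% vs 0% |
| 10% | 56.8% | 81% | 10% vs 0% |
| 20% | 61.6% | 81% | 20% vs 0% |
| 40% | 71.2% | 81% | 40% vs 0% |
| 60% | 80.8% | 81% | 60% vs 0% |

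**Step 3: break-even.** The arms are equal when 0.48(1 − *h*) = 0.19, so *h* = 1 − 0.19/0.48 = 60.4%. At 61.7% vs 81.0%, *h* = 1 − 0.19/0.383 = 50.4%. A background rate *b* of other moderate events common to both arms multiplies both remainders by (1 − *b*) and cancels, so the break-even stays the same.

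**Step 4: would it look like a finding?** The article names no test for this scale. Assume a two-sided 5% comparison of the proportions at Level 3 or higher, 154 per group, at 52% vs 81%. The chance of a significant result favouring MD is about 97% at *h* = 20%, 83% at 30%, 52% at 40% and 19% at 50%.

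**Step 5: grade 1 cytopenia.** Read literally, a grade 1 count is also an abnormality. Let *g* be the fraction of each arm's remaining patients (19% in control, 48% in MD) who have grade 1. The break-even becomes 1 − 0.19(1 − *g*_control) / [0.48(1 − *g*_MD)]. It is unchanged if the two fractions are equal, falls if grade 1 is more common among the MD remainder, and rises in the opposite case. The article gives no grade 1 rates, so the 60% figure cannot be carried over to that reading.

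No rate is given for the placebo-plus-moxibustion arm, so nothing can be computed for the comparison that isolates the decoction.

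**Level 4 alongside the other sections.** Its two parts are joined by a semicolon, and the article does not say whether both are needed. If stopping the study is required, a patient with a serious reaction who stays on study has no clear level. If a markedly abnormal indicator is enough, grade 3–4 cytopenia could also enter Level 4. The primary outcomes call such cytopenia an SAE, while the rhG-CSF section provides for treating it: "Patients with grade 2 or above myelosuppression should receive rhG-CSF treatment until the WBC count and ANC return normal". The article does not say which reading applies.

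**The case against.** The strongest reply is that the trial's safety evidence does not rest on this scale. Burns, skin reactions, heat syndrome and liver and kidney function are recorded as adverse events. Adverse effects are CTCAE-graded, and Table 3 schedules adverse events at every cycle and follow-up visit. The scale is not listed as a primary or secondary outcome, and no test is named for it. All of this stands, and it limits the point to conclusions drawn from the scale itself.

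The size is also open to challenge. The scale sits under Long-term efficacy without a time point, so levels might be assigned at the later visits, after counts have recovered, and the bias would then be smaller. The wording of Levels 2 and 3 turns on whether treatment can continue, which suggests use during treatment but does not settle it. If levels are given per indicator, blood counts cannot hide a liver or kidney signal. These objections weaken the figures. They do not explain why an efficacy measurement belongs among the safety indicators, or why this section merges what Table 3 keeps apart.

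A reader might go further and infer that the arm with less myelosuppression is bound to be rated safer whatever harm it causes, or that the trial cannot tell intervention harm from chemotherapy toxicity. The documents support neither. Moderate reactions reach Level 3, and serious reactions that end participation reach Level 4, whatever the counts, and harm above the break-even reverses the ranking. The separate adverse event records allow the harms to be told apart. Nor does the SAE label in the primary outcomes by itself make grade 3–4 cytopenia a Level 4 event, since the article never links the two.

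**Conclusion.** The point holds in limited form. As written, the scale mixes efficacy with safety. It can rate an arm with less myelosuppression as safer, and it can mask moderate intervention harm at Level 3 or higher.

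Under the stated assumptions the distortion is large: a 29-point advantage before any harm is counted, and a break-even between about 50% and 60% harm depending on which planning rates are used. These figures are illustrative. They would shrink if levels are assigned after counts recover, and they would change if grade 1 cytopenia counts. The primary analysis is unaffected, and so is the separate adverse event reporting. What is at risk is a statement that one arm is safer when it is drawn from this scale. The Level 4 wording is a secondary matter of reconciliation.

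**What to change.** - In the safety evaluation under Long-term efficacy, exclude WBC and ANC from the indicators behind the four levels. They are already analysed as primary outcomes.
- Base the between-arm comparison of harms on each patient's highest CTCAE grade for each event type, and show burns, skin reactions, heat syndrome and liver and kidney abnormalities separately.
- Reconcile the Level 4 wording with the primary outcomes and the rhG-CSF section, so that it is clear whether both of its parts are needed and how grade 3–4 cytopenia treated on study is classified. The choice of rule is for the investigators.

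The data are already collected. The cost is some rewording, a few more safety tables, and the loss of a single summary level that includes WBC and ANC.
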